#### 2.6.2. The Secondary Outcomes

Actigraphy (wActiSleep-BT, Actigraph LLC, Pensacola, USA), which is worn on the patient's wrist, can monitor the quality of sleep, such as sleep onset, sleep latency, total sleep time, sleep awakenings during the night, duration of sleep, and sleep efficiency. The software ActiLife6 (Version 6.8.1, Actigraph LLC) will be used to analyze every participant's sleep condition recorded in the Actigraphy.The Hamilton Rating Scale for Depression (HAMD), an observer-rating questionnaire with 17 items is used to describe the severity of cognitive and bodily symptoms of depressive disorders [25]. Each item is rated in 3- or 5-point scales. The higher total score indicates the severer depression.Self-Rating Depression Scale (SDS) is a self-rated scale to assess the severity of depressive adults [26]. The standard score is the integer part of 1.25 times of the raw score added up by the total 20 questions. The standard score of more than 53 points means the subject has depressive symptoms. The higher the score is, the more serious the depression is.

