## Abstract

*Background*. Depression is frequently accompanied by sleep disturbances including insomnia. Insomnia may persist even after mood symptoms have been adequately treated. Acupuncture is considered to be beneficial to adjust the state of body and mind and restore the normal sleep-awake cycle. This trial is aimed at evaluating the efficacy and safety of electroacupuncture on treating insomnia in patients with depression.* Methods*. We describe a protocol for a randomized, single-blinded, sham controlled trial. Ninety eligible patients will be randomly assigned to one of 3 treatment groups: treatment group (acupuncture), control A group (superficial acupuncture at sham points), and control B group (sham acupuncture). All treatment will be given 3 times per week for 8 weeks. The primary outcome is the Pittsburgh Sleep Quality Index (PSQI). The secondary outcomes are sleep parameters recorded in the Actigraphy, Hamilton Rating Scale for Depression (HAMD), and Self-Rating Depression Scale (SDS). All adverse effects will be accessed by the Treatment Emergent Symptom Scale (TESS). Outcomes will be evaluated at baseline, 4 weeks after treatment, 8 weeks after treatment, and 4 weeks of follow-up.* Ethics*. This trial has been approved by the Ethics Committee of Shanghai Municipal Hospital of Traditional Chinese Medicine (2015SHL-KY-21) and is registered with ChiCTR-IIR-16008058.

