Acupuncture, as a widely recognized alternative therapy in clinical practice, has been used to treat depressive disorders and related sleep disturbances recently. According to the theory of traditional Chinese medicine, acupuncture provides overall coordination, helping to achieve the state of relative equilibrium of body and mind and to restore the normal sleep-awake cycle. Researchers believe that electroacupuncture (EA) treatment can promote the sleep quality by direct manipulation of autonomic nervous system (ANS) [13]. In addition, some trials have investigated that EA can improve depressive disorders caused by cancer [14] or poststroke [15] and can act on depression by protecting nerve cells in the hippocampus [16]. Although the number of studies on depression or insomnia by acupuncture increases every year, there is little focus on the effects of EA on comorbid depression and insomnia and the quality of these related RCTs remains stagnant due to the methodological limitations that reduce the credibility of the results [17].

To study the clinical effects of electroacupuncture on treating insomnia and alleviating depression and to resolve some logic problems of present acupuncture researches, we design this randomized, parallel-group, and single-blinded clinical trial with a sufficient follow-up period. As a preliminary experiment, we aim at observing the effects of EA treatment on sleep status by subjective and objective assessments and eliminating the placebo effect of EA by setting reasonable sham acupuncture method as well. The results will be helpful to demonstrate if EA is an effective and safe therapy for improving sleep quality and mental health for patients with depression. The findings will be shared with the healthcare professionals, general public, and relevant organizations through publication of manuscripts and conference presentations.

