## 3. Discussion

Insomnia has been identified as the most common condition comorbid to depressive disorders [27]. The relationship between insomnia and mood symptoms is bidirectional in that poor sleep can precede an episode of major depressive disorder, and depressive mood can disrupt normal sleep patterns [4]. As research continues, some experts have suggested that comorbid insomnia and depression may have a different clinical course than either condition alone and may thus require specific treatment procedures. Electroacupuncture has been used as a complementary treatment to relieve unhealthy mood [28] and to normalize sleep disturbance [29] but the few studies focus on its efficacy and safety for treating comorbid depression and insomnia.

The main goal of our trial is to present a well-designed trial to study the therapeutic effect of EA on insomnia in depressive patients and overcome some methodological challenges in previous acupuncture clinical researches. Previous RCTs about acupuncture for depression or insomnia had limitations including imperfect blinding method, illogical design, or practical difficulty. To reach the goal, we design this strictly randomized controlled trial, setting two control groups to, respectively, apply sham acupoints and sham acupuncture method so that the result may help other researchers have better understanding about the effects of EA and the certain specificity of acupoints on treating insomnia and alleviating depression. In addition, we use single-blinded method to reduce test bias and ensure the reliability of the research.

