The key technical issues that need to be solved in this trial are (1) the application of the sham acupuncture method and (2) the challenge of patient compliance. All acupuncturists should accept training for several times before the trial begins to ensure the implementation of the sham acupuncture techniques and prepare for reasonable explanation in case of being questioned by patients in control B group. Patients' compliance is a common issue existing in various clinical trials. Good compliance is the central premise to help the trial move forward. Therefore, we will strengthen the publicity and education of medical knowledge to patients and improve healthcare in all aspects. For instance, appointments should be made by phone or email to establish the reservation system; reasonable arrangement of consultation time should be made to increase the patients' attendance rate; professional researchers will conduct family follow-up observation to supervise its implementation; and free acupuncture treatment will be promised by acupuncturists if the patients are not satisfied with the results of their treatment after the trial.

The limitation of this trial is the single-blinded method. Different from the placebo medicine trial, it is inevitable for the acupuncturists to know well about the real or sham acupuncture treatment and its possible effects. This is the reason why we apply the eye mask for the patients, use drape for separation during treatment, and set up training program for the acupuncturists.

We will standardize point selection, manipulation, needling instrument, and therapists' clinical experience in accordance with the STRICTA to ensure quality control of our acupuncture treatment. The objectively recognized assessment will improve the reliability of efficacy evaluation. We expect that this study will provide more credible evidence for the effects of EA on insomnia and depression and make up for the deficiencies in the current methodology of acupuncture clinical trials.

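### The HAMD total read as depression severity probably also scores insomnia, so a sleep-only effect could contribute to an apparent depression effect; a sleep-free HAMD score should be prespecified beside it

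*Protocol article*

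**What the plan says.** Section 2.6.2 makes the HAMD and the SDS secondary outcomes and defines both by their totals.

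- **HAMD:** "an observer-rating questionnaire with 17 items is used to describe the severity of cognitive and bodily symptoms of depressive disorders". On scoring it says "Each item is rated in 3- or 5-point scales" and "The higher total score indicates the severer depression".
- **SDS:** "The standard score is the integer part of 1.25 times of the raw score added up by the total 20 questions". A higher score again means worse depression.

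Neither entry names a subscale or a score that leaves out sleep items.

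Depression is presented as an effect of interest beside insomnia in three places. The Background gives the purpose as "To study the clinical effects of electroacupuncture on treating insomnia and alleviating depression". The Discussion hopes to inform others about "the effects of EA and the certain specificity of acupoints on treating insomnia and alleviating depression" and closes with the expectation that "this study will provide more credible evidence for the effects of EA on insomnia and depression".

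Section 2.1.1 requires an insomnia complaint and a PSQI above 7, together with a DSM-IV diagnosis of depression and a HAMD of 20 to 35. The PSQI is the primary outcome. Section 2.8 compares measurement data by t-test at a two-sided 5% level.

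**The concern.** The article attaches two conclusions to its outcomes: electroacupuncture improves sleep, and it relieves depression. The second depends on scales that, in their standard form, also score sleep.

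In an ordinary depression trial this matters little, because sleep disturbance is one symptom among many. Here everyone is enrolled for insomnia and the treatment is aimed at it, so the overlapping items are the ones most likely to move. The Background itself says that insomnia often outlasts adequate treatment of mood, so it treats the two as separable.

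A gain in sleep with no gain in mood is therefore a plausible result. It would show as a lower HAMD total, which the article reads as less severe depression. At stake is how one secondary result is interpreted; the primary comparison is not involved.

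**Working it through.** **Inputs from the article.** Two-sided 5% t-test (section 2.8); 24 per group in the reference study, 20% dropout and 30 per group (section 2.2); 17 HAMD items and 20 SDS items, SDS multiplier 1.25 (section 2.6.2); HAMD 20-35 at entry (section 2.1.1).

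**Assumptions, not in the article.**
- HAMD-17: three insomnia items scored 0-2, so 6 points of a 52-point maximum.
- SDS: one sleep item scored 1-4.
- Between-patient SD: 4-7 for the HAMD and 8-12 for the SDS.
- Sleep-item difference between arms: 1, 2 or 3 points on the HAMD.

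**The plan's own figure.** 24/(1 - 0.20) = 30 per group, which reproduces. This is only the dropout step: the article gives no effect size, SD or power. I use 24 and 30 per arm as the range.

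**Share of the HAMD.** 6/52 = 11.5% of the maximum. Against the entry limits, the items could supply at most 6/20 = 30% or 6/35 = 17%.

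**Chance that a sleep-only difference is significant on total HAMD.** Suppose mood is unchanged and the arms differ by δ points, all from the insomnia items. By the normal approximation,

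power = Φ( δ / (SD × √(2/n)) - 1.96 ).

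Example with n = 24, SD = 6, δ = 2: the standard error is 6 × √(2/24) = 1.732; 2/1.732 = 1.155; Φ(1.155 - 1.96) = Φ(-0.805) = 0.21.

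| Assumed SD | 1 point (n = 24 / 30) | 2 points | 3 points |
|---|---|---|---|
| 4 | 14% / 16% | 41% / 49% | 74% / 83% |
| 5 | 10% / 12% | 28% / 34% | 55% / 64% |
| 6 | 8% / 9% | 21% / 25% | 41% / 49% |
| 7 | 7% / 8% | 17% / 20% | 32% / 38% |

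The ranges are 7-16%, 17-49% and 32-83%. With no difference at all, the same formula gives Φ(-1.96) = 2.5% in favour of electroacupuncture. An exact t-test calculation gives nearly the same ranges: 8-16%, 16-48% and 31-81%. These are chances per comparison.

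**SDS.** The item can move by at most 3 raw points, or 1.25 × 3 = 3.75 standard points. With SD 8-12 and 24-30 per arm, the same formula gives 6-9% for 1 raw point (1.25 standard points), 11-23% for 2 raw points (2.5) and 19-44% for the full 3 raw points.

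**The case against.** Several objections carry weight.

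**Item content is not in the documents.** This is correct. The nearest the article comes is its reference to bodily symptoms. The overlap is an assumption about two named standard instruments, which the sponsor can check against its own rating forms.

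**Totals are conventional, and item-level analyses may sit in a full protocol or SAP.** This is also fair, and the absence of such an analysis from an article would not be a point by itself. What remains is that the article positively defines the total as the depression measure and names relief of depression as an effect separate from relief of insomnia.

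**The outcome is secondary and the trial is called preliminary.** True, and it limits the weight of the point.

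A reader might also infer four stronger claims that the documents do not support:

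- *A pure sleep effect would be reported as relief of depression.* At 1 or 2 points the chance stays below 50% at every SD tried. Only a large sleep-item gain makes it likely.
- *The HAMD and SDS are equally affected.* On the assumed content, 19 of the 20 SDS items do not score sleep, and even the full range of the one item stays below 45%.
- *The planned outcomes cannot tell the two effects apart.* The PSQI, actigraphy, HAMD and SDS are taken at the same four time points. A gain on the PSQI and actigraphy with little change on the SDS would hint at a sleep-only effect, though imperfectly.
- *Insomnia alone could carry patients over the HAMD entry threshold.* Section 2.1.1 also requires a DSM-IV diagnosis, and the randomised comparison does not depend on how entry scores are made up.

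**Conclusion.** The point holds in a limited form. The plan reads the HAMD total as depression in a sample selected for insomnia and states a depression aim apart from the sleep aim. An effect confined to sleep could therefore contribute materially to a significant HAMD difference. The size depends on how far the sleep items move: at 1 point the contribution is slight, at 2 points it is appreciable, and at 3 points it ranges from about one trial in three to more than four in five. The SDS overlap is minor.

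This rests on standard HAMD-17 and SDS content, an unchanged mood score, and SDs that the article does not give. It would not show that a HAMD effect is spurious, only that the total cannot attribute the effect to mood without further analysis. It is a worthwhile and inexpensive improvement to a secondary outcome, and it leaves the primary PSQI analysis, entry criteria and sample size as they are.

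**What to change.** In section 2.6.2, add that the HAMD total without its insomnia items will be analysed beside the full total, by the same method and at the same time points. Add that a depression effect separate from sleep will be claimed only if the sleep-free score supports it. The same may optionally be done for the SDS. Fix this before results are seen, since a sleep-free score added afterwards would be post hoc.

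The cost is a sentence or two and a second scoring of ratings that already make up the total. The article does not say whether item scores or only totals are entered in the database, so item-level entry should be confirmed.

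The reduced score is less comparable with published totals, which is why the full totals are kept. A non-significant sleep-free result should be read as unproven, not as evidence of no mood effect: at 80% power, 24-30 per arm detects only a difference of 0.81-0.72 SD, from (1.96 + 0.84) × √(2/n).

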#### 2.6.3. Adverse Events

Any adverse event (described as unfavourable or unintended signs, symptoms, or diseases occurring during the trial) related to the intervention or administration of SSRIs will be reported by patients and practitioners and accessed by the Treatment Emergent Symptom Scale (TESS) which is used as an associated indicator to mainly evaluate the safety of acupuncture treatment in this trial.

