## 2. Methods/Design

### 2.1. Setting and Design

We will conduct a single-center, patient-assessor-blinded, randomized controlled trial to evaluate the efficacy and safety of electroacupuncture for insomnia in patients with depression. The trial will be performed at the acupuncture department in Shanghai Municipal Hospital of Traditional Chinese Medicine in Shanghai, China. We will recruit 90 patients who meet inclusion criteria and randomly assign them to one of 3 groups, receiving electroacupuncture, superficial acupuncture at sham acupoints, or sham acupuncture. After one week of washout period, patients will accept 12 weeks of observation (Table 1). All treatment will be given 3 times a week (every other day) for 8 weeks. Participants will be assessed at 4 time points, the baseline (1 week before treatment), the middle of the treatment (4 weeks after treatment starts), end of the treatment (8 weeks after treatment starts), and follow-up (4 weeks after treatment finishes). All participants will complete the assessments by the PSQI, Actigraphy, HAMD, SDS, and TESS. We will follow the Standards for Reporting Interventions in Clinical Trials of Acupuncture (STRICTA) [18] throughout the trial.

Figure 1 is a flowchart of the study.

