## Figures and Tables

**Figure 1 fig1:**
[figure not shown]
Flowchart of the trial. PSQI: Pittsburgh Sleep Quality Index; HAMD: Hamilton Rating Scale for Depression; HAMA: Hamilton Rating Scale for Anxiety; SDS: Self-Rating Depression Scale; TESS: Treatment Emergent Symptom Scale.

**Table 1 tab1:** Trial process chart.

	Baseline	Treatment phase			Follow-up phase
	Week 1	Week 0	Week 4	Week 8	Week 4
*Patients*					
Enrollment	×				
Signed informed consent		×			
Medical history	×				
Merger disease	×				
Randomization		×			
Intervention			×	×	
*Primary outcomes*					
PSQI	×		×	×	×
*Secondary outcomes*					
Actigraphy	×		×	×	×
HAMD	×		×	×	×
SDS	×		×	×	×
TESS			×	×	×
SSRIs dose record	×		×	×	×
Patients' compliance			×	×	×

**Table 2 tab2:** Acupuncture method for each acupoint.

Number	Acupoint	Needling method	Needles
1	Baihui (GV20)	The angle between the needle tip and the scalp is 30 degrees. Move the needle tip backward along the anterior-posterior midline, and then insert the needle for 0.5 cun.	0.3 *∗* 40 mm
2	Shenting (GV24)	The angle between the needle tip and the scalp is 30 degrees. Move the needle tip backward along the anterior-posterior midline, and then insert the needle for 0.5 cun.	0.3 *∗* 25 mm
3	Yintang (GV29)	Pinch the local skin, and then puncture obliquely for 0.5 cun	0.3 *∗* 25 mm
4	Anmian (EX-HN22)	The angle between the needle tip and the scalp is 30 degrees. Puncture perpendicularly for 0.5 cun with the needle tip to the nose tip.	0.3 *∗* 40 mm
5	Shenmen (HT7)	Puncture perpendicularly for 0.5 cun.	0.3 *∗* 25 mm
6	Sanyinjiao (SP6)	Puncture perpendicularly for 1 cun.	0.3 *∗* 40 mm
7	Neiguan (PC6)	Puncture perpendicularly for 0.5 cun.	0.3 *∗* 40 mm

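### Adverse event reporting is limited to events related to the intervention or SSRIs, and the text and Table 1 disagree on whether TESS is taken at baseline

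*Protocol article*

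**What the plan says.** **Reporting rule.** Section 2.6.3 of the protocol article first defines an adverse event broadly: "described as unfavourable or unintended signs, symptoms, or diseases occurring during the trial". The same sentence then narrows what is reported to events "related to the intervention or administration of SSRIs will be reported by patients and practitioners". It names no assessor or procedure for deciding relatedness, and nothing else in the article provides for unrelated events. TESS is then described as "used as an associated indicator to mainly evaluate the safety of acupuncture treatment in this trial". The Abstract has a looser version: "All adverse effects will be accessed by the Treatment Emergent Symptom Scale (TESS".

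**Who knows the arm.** Section 2.4 says that everyone except the acupuncturists is blinded, and that acupuncturists take no part in outcome assessment.

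**TESS schedule.** Section 2.1 reads "Participants will be assessed at 4 time points, the baseline (1 week before treatment" and goes on to list the middle of treatment, its end, and follow-up. The next sentence is "All participants will complete the assessments by the PSQI, Actigraphy, HAMD, SDS, and TESS", with no exception for any visit. The Abstract likewise has "Outcomes will be evaluated at baseline, 4 weeks after treatment, 8 weeks after treatment, and 4 weeks of follow-up". In Table 1 ("Trial process chart"), TESS sits under the secondary outcomes. Its row is blank at baseline and week 0, and marked at week 4, week 8 and follow-up.

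**The concern.** Evaluating safety is a stated aim in both the Abstract and section 2.1, and TESS is the main instrument for it. Two features of the plan weaken that evaluation.

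First, a relatedness condition placed on reporting, and not applied afterwards, asks the reporter to settle causation before the event is on record. An event wrongly thought unrelated cannot be recovered later. If any of the reporters know the allocation, the threshold may also differ between arms. The treatment arm has needle manipulation and electrical stimulation, whereas in control B no needle enters the skin, so a practitioner could readily attribute the same complaint differently.

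Second, entry requires a HAMD score of 20–35 and a PSQI above 7, and SSRIs are permitted, so symptoms before the first session are plausible. Without a TESS score from before treatment, a symptom seen at week 4 cannot be classed within that patient as new, worsened or long-standing.

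**Working it through.** **1. Arm size.** The article's only computed figure is the sample size in section 2.2. From 24 per group and 20% dropout, 24 / (1 − 0.20) = 30 per group, and 3 × 30 = 90. This matches the plan. It supplies the arm size used below and is not itself in question.

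**2. Text against table.**

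| Instrument | Section 2.1 | Table 1, baseline | Week 4 | Week 8 | Follow-up |
|---|---|---|---|---|---|
| PSQI, Actigraphy, HAMD, SDS | listed | marked | marked | marked | marked |
| TESS | listed | blank | marked | marked | marked |

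Section 2.1 treats the five instruments alike, while Table 1 treats TESS differently. Section 2.1 implies a baseline TESS only when its two adjacent sentences are read together; it does not say so outright. The two places need reconciling.

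**3. Effect of the reporting condition (assumed rates; the document gives none).** Take a true event rate of 20% in each of two arms of 30, so 30 × 0.20 = 6 expected events per arm. Reported events = 6 × share attributed.

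| Share attributed, EA vs sham | Reported events | Reported rate |
|---|---|---|
| 50% vs 50% | 3.0 vs 3.0 | 10% vs 10% |
| 80% vs 50% | 4.8 vs 3.0 | 16% vs 10% |
| 80% vs 20% | 4.8 vs 1.2 | 16% vs 4% |

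Events are lost in every row. A false difference appears only where attribution differs by arm.

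**4. Effect of having no baseline TESS (assumed rates).** Let b be the prevalence of a symptom before treatment, and let the new-symptom rates be e1 = 30% and e0 = 10%. On-treatment prevalence is p = b + (1 − b)e, so the visible difference is (1 − b)(e1 − e0) = 0.20(1 − b). With n = 30 per arm and a two-sided 5% test, power = Φ[(d − 1.96·SE0)/SE1]. Here d = p1 − p0, SE0 = √(2p̄(1 − p̄)/n) with p̄ the mean of p1 and p0, and SE1 = √((p1(1 − p1) + p0(1 − p0))/n).

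| b | p1 vs p0 | Difference | Power |
|---|---|---|---|
| 0% | 30% vs 10% | 20 points | 49% |
| 20% | 44% vs 28% | 16 points | 25% |
| 40% | 58% vs 46% | 12 points | 15% |
| 60% | 72% vs 64% | 8 points | 10% |

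For b = 40%: p̄ = 0.52, SE0 = 0.1290 and SE1 = 0.1281, so (0.12 − 0.2528)/0.1281 = −1.04 and Φ = 0.15.

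A baseline would not restore the full 49% for a single symptom, because patients who already have it cannot newly develop it. At b = 40%, 30 × 0.60 = 18 per arm are at risk. Then SE0 = √(0.32/18) = 0.1333 and SE1 = √(0.30/18) = 0.1291, so (0.20 − 0.2613)/0.1291 = −0.475 and power is about 32%. On this assumption a baseline roughly doubles power, from 15% to 32%.

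**5. The two illustrations are alternatives.** Step 3 supposes that the relatedness condition acts on what is recorded. Step 4 supposes that every symptom present is scored on TESS. If the condition also screened TESS entries, many existing symptoms would not be scored. The article does not say which applies, so the two effects should not be added together.

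**The case against.** A reader might infer that the safety comparison has no reference level at all. The document does not support that. Three arms are randomised 1:1:1, so the sham arms are a concurrent reference. What may be missing is the within-patient reference, and only if Table 1 governs. Starting a treatment-emergent scale after treatment begins is also a coherent reading of Table 1. If section 2.1 governs, the baseline exists.

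A reader might also infer that unblinded staff decide which events count. That goes further than the text. Section 2.6.3 names patients, who are blinded, ahead of practitioners. It does not say that the practitioners are the acupuncturists, although that is a natural reading, and it does not say that anyone formally judges relatedness. The absence of a causality procedure is no finding in itself, since an article commonly leaves that to the full protocol.

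Further, TESS is a scheduled scale for all participants, so section 2.6.3 could be read as spontaneous reporting of related events plus routine TESS. The definition confines adverse events to those arising during the trial, which does not invite counting earlier symptoms. Medical history, concurrent disease, SSRI dose, HAMD and SDS are all recorded at baseline.

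These points narrow the concern without removing it. Nothing cancels the relatedness condition: the Abstract speaks of adverse effects, and that word itself presupposes a cause. Baseline history and mood scales are not a TESS score item by item, so they cannot show which TESS symptoms are new.

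**Conclusion.** The concern holds in limited form. Section 2.6.3 states a reporting rule that can lose events attributed to neither the intervention nor SSRIs. The loss may be uneven across arms if the acupuncturists are among the reporters, which is likely but not stated. Separately, section 2.1 and Table 1 disagree on a baseline TESS. This is an unresolved inconsistency, not a proven absence.

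The size depends on rates the document does not give. Under the assumptions shown, unequal attribution could turn equal true rates into 16% versus 10%, or 16% versus 4%; equal attribution creates no false difference. If Table 1 governs and TESS scores all symptoms present, prior prevalence of 20% to 60% would cut a 20-point difference to between 16 and 8 points, and power from 49% to between 25% and 10%. Power is modest even without dilution, so these figures show direction and rough scale only. Both points should be corrected; neither invalidates the randomised comparison.

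**What to change.** 1. In section 2.6.3, delete the relatedness condition and record every adverse event during the trial. Keep relatedness as a separate field, completed after the event is recorded by the outcome assessors, whom section 2.4 already blinds.
2. Reconcile Table 1 with section 2.1 by marking TESS at the existing baseline visit.
3. Compare new or worsened TESS symptoms, relative to baseline, by arm.

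The cost is slightly more data entry, one extra form field, and one short scale at a visit that already takes place.
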